## Abstract

**Background:**

Chronic low back pain (cLBP) is a prevalent condition associated with poor rehabilitation outcomes and high recurrence rates. Previous studies suggest that the number, structure, and network patterns of trunk muscle synergy may contribute to this condition. Our previous research mapped the neural representation of cLBP trunk muscles in the primary motor cortex (M1) and identified a disrupted M1-trunk muscle synergy pattern. Recent studies indicate that the dorsolateral prefrontal cortex (DLPFC) has a key role in the internal connectivity of cLBP patients when coping with chronic pain. This study aims to determine whether transcranial direct current stimulation (tDCS) of the DLPFC in cLBP patients can enhance the activity and functional connectivity of M1 and DLPFC, thus improving abnormal trunk muscle synergy.

**Methods:**

This study is a randomized, double-blind, controlled trial. Forty-eight individuals aged 20 to 55 years with cLBP will be randomly assigned to receive either (1) a 3-week DLPFC-tDCS intervention (*n* = 24) or (2) a 3-week M1-tDCS intervention (*n* = 24), administered four times per week for a total of 12 sessions. Clinical outcomes will be assessed at baseline, 3 weeks, and 6 and 12 months after randomization. Primary outcomes include pain intensity, disability, and scores on the Hamilton Depression and Hamilton Anxiety scales. Secondary outcomes include surface electromyography characteristics of trunk muscles, oxygenated and deoxygenated hemoglobin concentrations in the M1 and DLPFC, and functional connectivity between these two brain regions. These outcomes will be evaluated before and after the intervention. Effect sizes and a mixed-model repeated measures analysis of variance (2 groups × 4 time points) will be calculated.

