#### Sample size

2.5.3

Based on the following formula and our preliminary experimental results of the primary outcome measures (VAS), with a significance level of *α* = 0.05, test power (1-*β*) = 0.9, a mean difference of 1.15, and a variance index of 1.48, it was determined that 20 participants per group are required. To account for an estimated attrition rate of 120%, a total of 48 cLBP participants will be recruited. To compare the effects after the intervention of the two groups, twenty-four right-handed healthy individuals with no history of cLBP were recruited.

$$N={\left[\frac{(t_{\alpha ∕2}+t_{\beta })S}{\delta }\right]}^{2}$$

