##### Pain intensity

2.10.1.1

Pain intensity will be assessed using the VAS, which ranges from 0 to 10 cm, where “0 cm” indicates no pain and “10 cm” represents unbearable pain. Moreover, the Short-Form McGill Pain Questionnaire (SFMPQ) will be used to evaluate each participant’s pain experience (Strand et al., 2008). The SFMPQ consists of 15 items divided into two categories: affective scores (4 items) and sensory scores (11 items). Each item is rated on an intensity scale from 0 to 3 (0 = none, 1 = mild, 2 = moderate, 3 = severe). Pain assessments will be conducted at all time points, including baseline, 3 weeks, 6 months, and 12 months post-randomization. Meanwhile, during the follow-up period, we will record whether the patients are using painkillers or other treatments.

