##### Disability

2.10.1.2

Disability associated with cLBP will be measured using the Oswestry Disability Index (ODI), a validated tool consisting of 10 questions, each with 6 response options scored from 0 to 5. This index evaluates functional impairment in cLBP by incorporating pain and physical activity measures. Based on the total score, disability is categorized as bed-ridden (81–100%), crippled (61–80%), severe disability (41–60%), moderate disability (21–40%), or minimal disability (0–20%) (Martí-Salvador et al., 2018). Participants will be instructed to complete the questionnaire based on their condition on the day of assessment.

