##### Mental health

2.10.1.3

Mental health will be assessed using the short version of the Hamilton Depression Scale (HDS) and the Hamilton Anxiety Scale (HAMA). The HDS consists of three subscales, each comprising seven items, designed to evaluate anxiety, depression, and stress over the previous week (Kaptan et al., 2012). Responses are rated on a scale from 0 to 3 (fully disagree to fully agree), with total scores indicating symptom severity: a score of 13 or higher suggests depressive symptoms, 14–27 indicates mild depression, 28–41 reflects moderate depression, and scores of 42–53 suggest high level depression. The HAMA is primarily used to evaluate the severity of anxiety symptoms in individuals with neurosis and other conditions. It evaluates 14 aspects of anxiety, including mood, depressive mood, cognitive function, insomnia, fear, tension, somatic anxiety, reproductive and urinary symptoms, gastrointestinal and digestive symptoms, respiratory symptoms, cardiovascular symptoms, sensory symptoms, and behavioral responses during social interactions (Yin et al., 2023).

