#### Statistical analysis

2.11.1

Statistical analyses will be performed using SPSS (version 25.0, IBM, USA). Before performing descriptive statistics, the Shapiro–Wilk test will be applied to evaluate the normality of data distribution. Data following a normal distribution will be reported as mean and standard deviation (SD), while non-normally distributed data will be expressed as medians with interquartile range (IQR). Categorical variables will be summarized as percentages and frequencies. Baseline demographic and clinical characteristics will be compared between groups using appropriate statistical tests based on the data type. Continuous variables that follow normal distribution will be analyzed while using independent sample *t*-tests, whereas non-parametric Mann–Whitney *U*-tests will be applied for non-normally distributed continuous data. Categorical variables will be analyzed using chi-square tests or Fisher’s exact tests, as appropriate. Correlations between variables will be evaluated using the Pearson correlation coefficient or Spearman correlation coefficient based on the type of data. A repeated-measures analysis of variance (2 groups × 4 time points) will be performed to assess the therapeutic effects on primary and secondary outcomes. If a significant main effect was observed, *post hoc* tests with Bonferroni correction were conducted. A *p*-value of <0.05 will be considered statistically significant.

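### Four primary domains measured by five instruments are each tested at p < 0.05 with no hierarchy or correction across them, although the sample size spends the full 0.05 on VAS alone

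*Protocol article*

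**What the plan says.** - **Abstract, Methods:** "Primary outcomes include pain intensity, disability, and scores on the Hamilton Depression and Hamilton Anxiety scales". No one of them is singled out.
- **Section 2.10.1 (Primary outcome measures):** pain is measured twice. "Pain intensity will be assessed using the VAS, which ranges from 0 to 10 cm", and in addition "the Short-Form McGill Pain Questionnaire (SFMPQ) will be used to evaluate" the pain experience. Then "Disability associated with cLBP will be measured using the Oswestry Disability Index (ODI"), and "Mental health will be assessed using the short version of the Hamilton Depression Scale (HDS) and the Hamilton Anxiety Scale (HAMA"). That makes five instruments in four domains, unranked.
- **Section 2.1:** the primary evaluation is set at 3 weeks.
- **Section 2.5.3:** the sample size rests on "our preliminary experimental results of the primary outcome measures (VAS"), with alpha 0.05, power 0.9, a mean difference of 1.15 and a spread of 1.48. No other instrument has an assumed effect or a power.
- **Section 2.11.1:** one repeated-measures ANOVA (2 groups by 4 times) serves primary and secondary outcomes alike, and a p-value "of <0.05 will be considered statistically significant". Bonferroni is mentioned once, for post hoc tests after a significant main effect.
- **Introduction, objectives:** pain, disability and mental health come under the secondary objective. The comparative hypothesis names M1-DLPFC connectivity and symptoms of depression and anxiety.

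**The concern.** A primary outcome fixes in advance which result decides the trial. Here five instruments share that label and the threshold is 0.05 for each. There is no testing order, no division of alpha and no requirement that all must succeed. The one stated correction is attached to follow-up comparisons after an ANOVA, not to the set of primary outcomes. Meanwhile the sample size gives the whole 0.05 to VAS, as if it were the only primary.

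With 48 patients, one isolated p < 0.05 among the five could be reported as the primary finding, and nothing in the protocol would stop a reader from accepting it at face value. The chance of such a result when neither stimulation site is better would exceed 5%.

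**Working it through.** **1. The plan's own figure.** Section 2.5.3 prints N = [(t_α/2 + t_β)S/δ]². Take S = 1.48 and δ = 1.15.

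- Normal quantiles: [(1.960 + 1.282) × 1.48/1.15]² = 17.4, so 18.
- t quantiles on 19 df: [(2.093 + 1.328) × 1.48/1.15]² = 19.4, so 20.

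The stated 20 per group is reproduced, and 20 × 1.2 = 24 per group gives 48. The calculation uses two-sided alpha 0.05 for VAS with nothing held back for other outcomes.

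**2. Familywise error if any one omnibus test can carry the claim.** Assume one test per instrument at 0.05 and all nulls true.

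- Five independent tests: 1 − 0.95⁵ = 22.6%.
- Four independent tests (one per domain): 1 − 0.95⁴ = 18.5%.

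The instruments will be correlated, and the protocol gives no correlations. Simulating equicorrelated normal test statistics (1,000,000 draws each) gives:

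| Assumed correlation | Five tests | Four tests |
|---|---|---|
| 0.3 | 20.9% | 17.4% |
| 0.5 | 18.3% | 15.5% |
| 0.7 | 14.8% | 13.1% |
| 0.8 | 12.8% | 11.4% |
| 0.9 | 10.2% | 9.4% |

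**3. If the claim rests on a corrected 3-week contrast instead.** The 2 × 4 omnibus test does not isolate 3 weeks; a 3-week contrast appears only at the post hoc step. Section 2.11.1 does not define the Bonferroni family. Suppose it covers three or four time-point contrasts within each outcome.

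- Three contrasts: per-outcome level 0.05/3 = 0.0167, and 1 − (1 − 0.0167)⁵ = 8.1%.
- Four contrasts: per-outcome level 0.05/4 = 0.0125, and 1 − (1 − 0.0125)⁵ = 6.1%.

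Both are for five independent outcomes. Requiring a significant ANOVA first can only lower them.

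**4. After a correction.** One primary: 5%. Bonferroni at 0.05/5 = 0.01 across five independent tests: 1 − 0.99⁵ = 4.9%. Holm also holds the rate at or below 5%, and its power is never below Bonferroni's.

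**The case against.** **The analysis plan may settle this.** A general 0.05 threshold is compatible with adjusted p-values, and procedures across outcomes are often left to an analysis plan, which is not shown. This stands in part: such a rule may exist elsewhere. But the protocol is not silent. It states the test, the threshold and where the correction applies, and its flat list of primaries conflicts with a sample size built on VAS alone.

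**The inflation depends on a success rule that the protocol never states.** This stands. The protocol does not say that any one significant outcome is enough, does not give correlations and does not say whether the omnibus test or a 3-week contrast decides.

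**Five may be too many.** The Abstract lists four scores or domains, and SFMPQ shares the pain heading with VAS. This is fair, so both counts are shown above.

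**Stronger readings that the text does not support:**

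- *The false-positive rate is 15 to 23%.* That range needs five omnibus tests, success on any one, all nulls true and correlations no higher than 0.7.
- *HDS and HAMA sit at their floor because section 2.5.2 excludes mental illness.* The exclusion is undefined and no baseline scores are given.
- *Section 2.1 implies a single primary outcome.* It fixes a time point, which is compatible with several outcomes.

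**Conclusion.** The point holds. As written, the protocol does not control error across its primary outcomes and does not define which result makes the trial positive.

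The size is conditional. With success on any one omnibus test and all nulls true, the error runs from 22.6% for five independent tests to about 10% for five at correlation 0.9; counting four gives 18.5% to about 9%. That is roughly two to four and a half times the nominal 5%. If only a Bonferroni-corrected 3-week contrast counts, it is about 6 to 8% or less. No single value can be put on the trial, because the protocol supplies neither the correlations nor the decision rule. Under each of these readings except full correction across outcomes, the rate is not held at 5%.

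VAS is the outcome used for sizing, but a reader should not infer from this that its stated power is secured. The printed formula has the one-sample form, which is a separate matter.

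**What to change.** Choose one of two routes before any unblinded data are seen.

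**Route 1: one primary.** Name VAS at 3 weeks, the outcome used for sizing, as the single primary in the Abstract, 2.10.1 and 2.11.1. In 2.11.1, state the between-group comparison at 3 weeks that decides it. Make SFMPQ, ODI, HDS and HAMA secondary, tested by Holm or in a fixed order after VAS. Align the registry entry if it lists the same set.

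*Cost:* text changes only, with no extra patients or visits. Four instruments lose primary status. Two of them, HDS and HAMA, carry the clinical part of the comparative hypothesis in the Introduction, so the investigators may not want this route.

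**Route 2: several primaries.** If depression and anxiety must stay primary, list the retained instruments explicitly, apply Holm across them, and state that the power figure refers to VAS at unadjusted alpha.

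*Cost:* each test has less power. The lower limit for VAS among five is Holm's first step, 0.05/5 = 0.01. In a two-group comparison with SD 1.48 and 20 per group, the standardised effect is 1.15/(1.48 × √(2/20)) = 2.457. Power is Φ(2.457 − 1.960) = 69% at 0.05 and Φ(2.457 − 2.576) = 45% at 0.01. If 1.48 is a variance, the figures are 85% and 66%. Retaining fewer primaries reduces the loss.

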**Discussion:**

The results of this trial will clarify the efficacy of DLPFC-tDCS in enhancing M1-DLPFC functional connectivity and improving trunk muscle synergy patterns. These findings will provide a theoretical foundation for developing new therapeutic targets for the treatment of cLBP.

**Clinical trial registration:**

https://www.chictr.org.cn, identifier ChiCTR2300078887.

## Introduction

1

Low back pain (LBP) is a significant public health concern and a leading cause of disability worldwide, contributing to workplace absenteeism (Murray et al., 2012; Balagué et al., 2012). Chronic LBP (cLBP) is classified as nonspecific when no clear, identifiable cause is present and as chronic when it lasts longer than 12 weeks (Knezevic et al., 2021). An estimated 80% of adults have been reported to experience at least one episode of cLBP in their lifetime, with 40% developing a persistent form (Balagué et al., 2012; Zhou et al., 2024).

Various regions of the brain and spinal cord contribute to neuroplasticity in LBP, with research primarily focusing on the motor cortex (Brumagne et al., 2019). For instance, transcranial magnetic stimulation (TMS) over the primary motor cortex (M1) while monitoring trunk muscle activity has demonstrated changes in the stimulus–response profile of these muscles. This suggests neuroplasticity at M1 and changes in TMS-related trunk muscle activation (Tsao et al., 2008, 2011; Li et al., 2021). On the other hand, altered activation patterns in trunk muscles have been associated with movement avoidance behaviors due to perceived risk. These motor system adaptations may then affect spinal biomechanics. Previous studies indicate that during specific tasks, individuals with cLBP exhibit a reduction in trunk muscle synergy (Sung et al., 2019). Moreover, during symmetrical tasks, the trunk muscle synergistic network in cLBP patients has shown asymmetry (Rose-Dulcina et al., 2019; Lu et al., 2001). These results indicate that cLBP patients experience neuromuscular regulation dysfunction within the M1-trunk muscle synergy. Therefore, M1 has emerged as a potential therapeutic target for cLBP. However, recent reviews suggest that stimulation of M1 may not be effective in treating cLBP (Kandić et al., 2021). Furthermore, the dorsolateral prefrontal cortex (DLPFC) appears to play a key role in cognitive-behavioral processing and its association with chronic pain in cLBP patients (Kandić et al., 2021; Knotkova et al., 2021). This suggests that DLPFC could serve as an alternative target for top-down neural modulation in cLBP management.

Neuroadaptive changes in the central nervous system among cLBP patients are closely related to abnormal trunk muscle coordination patterns. Understanding the association between these trunk muscle functions and neurobiological changes is essential for optimizing treatment strategies. Non-invasive techniques, including electroencephalography, TMS, and functional magnetic resonance imaging (fMRI), have significantly contributed to advancing knowledge of brain function (Brumagne et al., 2019; Hodges and Danneels, 2019; Kenefati et al., 2023). However, their application in studying cortical dynamics during functional motor tasks is limited due to stringent environmental constraints, including the need for electromagnetic shielding, immobility requirements, and sensitivity to movement artifacts. To address these limitations, functional near-infrared spectroscopy (fNIRS) has emerged as a portable and non-invasive neuroimaging technique with unique advantages. fNIRS enables real-time monitoring of hemodynamic responses associated with neural activation through neurovascular coupling mechanisms (Ferrari and Quaresima, 2012). Moreover, fNIRS demonstrates greater resistance to environmental interference, allowing for the assessment of spatiotemporal characteristics of cerebral cortical activity during dynamic motor tasks.

Being another non-invasive technique, Transcranial direct current stimulation (tDCS) facilitates top-down neuromuscular regulation (Kandić et al., 2021). A fMRI study of healthy individuals showed that both M1-tDCS and DLPFC-tDCS increased the functional connection between M1-supplementary motor area (SMA), but only DLPFC-tDCS regulated the functional connection between M1-SMA-DLPFC. This indicates that M1-tDCS mainly regulates the functional connections of the motor sensory network, while DLPFC-tDCS can also regulate the functional connections related to cognition and emotion (Sankarasubramanian et al., 2017). However, whether tDCS effectively increases M1-DLPFC functional connectivity and improves abnormal trunk muscle synergy patterns in cLBP patients remains unclear.

This study primarily aims to assess the role of M1-DLPFC functional connectivity in regulating trunk muscle synergy patterns in cLBP patients. The primary hypothesis proposes that abnormal trunk muscle synergy in cLBP is associated with reduced M1-DLPFC functional connectivity. The secondary objective is to evaluate the effects of M1-tDCS and DLPFC-tDCS post-intervention and at follow-up in terms of (1) pain, (2) disability, (3) mental health, (4) surface electromyography characteristics of trunk muscles, and (5) the concentration of oxygenated and deoxygenated hemoglobin in the cerebral cortex of M1 and DLPFC. The secondary hypothesis is that DLPFC-tDCS is more effective than M1-tDCS in increasing M1-DLPFC functional connectivity and improving symptoms of depression and anxiety.

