#### fNIRS data analysis

2.11.3

The NirSpark software package will be employed to preprocess fNIRS data. Initially, raw fNIRS signals will be transformed into optical density changes by applying a logarithmic transformation. Channels with excessively low optical intensity (coefficient of variation > 10%) will be removed to eliminate noise. A bandpass filter will be applied to minimize physiological artifacts and instrumental noise, with high-pass and low-pass cut-off frequencies set at 0.01 Hz and 0.1 Hz, respectively. Changes in [HbR] and [HbO] concentrations will then be determined using the modified Beer–Lambert law. To analyze cerebral cortical activity during tasks, a general linear model (GLM) will be used, represented by the equation:

Δ[Hbx]=X×β+ε

where Y represents the variation in [HbR] or [HbO] concentration, X denotes the modeled neural response predicted based on task onset and convolved with a classical hemodynamic response function, β is the regression coefficient reflecting the activation level of each channel, and ɛ accounts for unexplained variability or noise in the data. The β-value (μmol), which quantifies activation at each channel, will be calculated alongside the standard errors for [HbR] and [HbO] in both groups for each trial.

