### Strengths and limitations

3.2

One of the major strengths of this protocol is that it represents one of the first clinical trials investigating the efficacy of DLPFC-targeted tDCS in patients with cLBP. If proven effective, DLPFC-tDCS could serve as a viable therapeutic option for managing cLBP. Another advantage of the study is its potential to reveal the neuroregulatory mechanisms underlying the functional connections between brain regions and their impact on trunk muscle coordination in cLBP patients.

However, there will be some limitations. A key limitation is the absence of a healthy control group. Including healthy participants would allow for a more comprehensive comparison with the M1-tDCS and DLPFC-tDCS groups, improving the interpretation of the results. Moreover, differences in the sampling rates of the two fNIRS systems used during measurements present a methodological challenge. Since the sampling rates of fNIRS and sEMG differ, direct correlation analyses between their signals cannot be performed. Instead, only data-level analyses can be conducted, which may limit the ability to fully capture the relationship between cortical activity and muscle activation patterns.

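### The primary hypothesis (M1-DLPFC connectivity and trunk muscle synergy) does not match the primary outcomes or the VAS-based sample size, and connectivity has no measure in the methods

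*Protocol article*

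**What the plan says.** **Objectives (Introduction, last paragraph).** The aim is stated as "This study primarily aims to assess the role of M1-DLPFC functional connectivity in regulating trunk muscle synergy patterns in cLBP patients", followed by "The primary hypothesis proposes that abnormal trunk muscle synergy in cLBP is associated with reduced M1-DLPFC functional connectivity". The clinical effects come second: "The secondary objective is to evaluate the effects of M1-tDCS and DLPFC-tDCS post-intervention and at follow-up in terms of (1) pain, (2) disability", continuing with mental health, trunk-muscle sEMG and cortical haemoglobin. The other hypothesis reads: "The secondary hypothesis is that DLPFC-tDCS is more effective than M1-tDCS in increasing M1-DLPFC functional connectivity and improving symptoms of depression and anxiety".

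**Outcomes.** The Abstract says "Primary outcomes include pain intensity, disability, and scores on the Hamilton Depression and Hamilton Anxiety scales", and section 2.10.1 agrees. The Abstract's secondary outcomes are sEMG characteristics, haemoglobin concentrations and "functional connectivity between these two brain regions". Section 2.10.2 lists muscle synergy and haemoglobin concentrations, then the tasks. It does not list connectivity between the two regions.

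**Sample size (2.5.3).** Based on VAS only: α = 0.05, power 0.9, difference 1.15, variance index 1.48, 20 per group, 48 recruited.

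**Analysis.** Section 2.11.1 plans a 2 × 4 repeated-measures ANOVA for primary and secondary outcomes, and Pearson or Spearman correlations with no variables named. In 2.11.3 the fNIRS output is a general linear model in which "β is the regression coefficient reflecting the activation level of each channel". The only connectivity methods described are intermuscular (2.11.2).

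**Reference group.** Section 2.5.3 says 24 healthy individuals were recruited. Section 3.2 lists the lack of a healthy control group as a key limitation.

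**The concern.** A trial's primary hypothesis should lead to a primary endpoint, a test and a sample size. Here the chain breaks at each link. The Introduction says the trial is chiefly about a brain-muscle association, while the Abstract, 2.10 and 2.5.3 describe a clinical comparison of two stimulation sites. VAS, the only outcome used for sizing, appears in neither hypothesis in the Introduction: the first concerns connectivity and synergy, the second concerns connectivity, depression and anxiety.

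Connectivity is central to both hypotheses, yet the methods never say how it is obtained. An activation coefficient describes how strongly a channel responds to the task. It does not describe how the signals of two regions move together.

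At stake is what the trial may conclude. If the clinical scales show no difference and some later-chosen connectivity index correlates with some synergy metric, a reader could not tell whether the primary question was answered or whether the result was selected afterwards.

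**Working it through.** **1. The hierarchy, side by side**

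| Quantity | Introduction | Abstract and 2.10 | 2.5.3 |
|---|---|---|---|
| Connectivity-synergy association | Primary aim and hypothesis | Not an outcome as such; synergy and fNIRS measures are secondary | Not used |
| Pain | Secondary objective; in neither hypothesis | Primary | VAS sizes the trial |
| Disability | Secondary objective; in neither hypothesis | Primary | Not used |
| Depression, anxiety | Secondary objective; secondary hypothesis | Primary | Not used |
| M1-DLPFC connectivity | In both hypotheses | Secondary in the Abstract; absent from 2.10.2 | Not used |

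**2. Does the planned analysis yield the quantity?** Section 2.11.3 goes from raw signal to optical density, channel rejection, a 0.01-0.1 Hz band-pass filter, haemoglobin changes and a GLM. The result is one β per channel for HbO and HbR. No step relates an M1 series to a DLPFC series. The 2 × 4 ANOVA in 2.11.1 compares arms over time and does not test an association across patients. The correlation sentence could cover one, but it names no pair.

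**3. The plan's own sample size.** Inputs from 2.5.3: S = 1.48 (read as an SD), δ = 1.15, two-sided α = 0.05, power 0.90. The printed formula is N = [(t_{α/2} + t_β)S/δ]².
- With normal quantiles: [(1.960 + 1.282) × 1.48/1.15]² = 17.4, so 18.
- With t quantiles iterated on n − 1 degrees of freedom: 20, as stated.
- 20 × 1.2 = 24 per group, 48 in total (reading the stated 120% as a factor of 1.2).

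The figure reproduces. It is a VAS calculation and contains no connectivity or synergy quantity.

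**4. What 48 patients could show on the primary hypothesis.** The documents give no expected correlation, so this is a range under assumptions: one pre-specified pair of measures, both arms pooled at baseline, two-sided α = 0.05, Fisher z approximation. Detectable |r| = tanh[(1.960 + z_power)/√(n − 3)].
- n = 48, 80%: tanh(2.802/√45) = tanh(0.418) = 0.395. At 90%: tanh(3.242/√45) = 0.449.
- n = 40 (2 × 20 completers), 80%: tanh(2.802/√37) = tanh(0.461) = 0.431. At 90%: tanh(3.242/√37) = 0.488.
- Power at n = 48: 27% for r = 0.2, 55% for 0.3, 81% for 0.4, 96% for 0.5.

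**5. Reference group.** The words *abnormal* and *reduced* in the hypothesis imply a comparison with people without cLBP. A correlation within patients can show that the two measures vary together. It cannot show that either departs from normal. Sections 2.5.3 and 3.2 contradict each other on whether the comparison group exists.

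**The case against.** The strongest reply is that this is a condensed article. Channel sets, the connectivity index and the correlation pairs are details that a full protocol or analysis plan commonly holds, and 2.10.2.2 refers to supplementary material for regions and channels. That has force for the finer details, and their absence alone would be no finding. It does not remove the contradiction between the Introduction and sections 2.10 and 2.5.3, nor the mismatch between the Abstract's outcome list and 2.10.2. Condensation is also a weak explanation here, since 2.11.3 gives filter limits and the model equation, and 2.11.2 names methods and a toolbox for connectivity between muscles.

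Three stronger readings are tempting but not supported:

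- **That the trial cannot answer its primary hypothesis.** Haemoglobin series are recorded continuously with M1 and DLPFC as the focus, synergy metrics are described, correlations are planned, and step 4 shows useful power for a moderate correlation. An index could be derived; the text does not define one.
- **That hundreds of tests are planned.** 102 channels × 2 chromophores = 204, and 204 × 0.05 = 10.2 expected false positives if every null holds. But no section says the whole array is tested channel by channel, and 2.10.2.2 says the focus is M1 and DLPFC.
- **That the sampling-rate limitation blocks the hypothesis.** Section 3.2 says that "direct correlation analyses between their signals cannot be performed", but goes on to allow analyses at data level. Correlating patient-level summaries fits within that, so the statement can stay.

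Nor are the primary outcomes pain alone; only the sample size is.

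**Conclusion.** The point holds as a contradiction in the current text. The Introduction ranks the connectivity-synergy association above the clinical effects, while the Abstract, 2.10 and 2.5.3 rank and size the trial the other way. Followed as written, the methods produce no M1-DLPFC connectivity value, so the primary hypothesis lacks a primary endpoint, a measure, a named test and a sample-size basis.

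The sample size is unjustified for that hypothesis but not hopeless: 80% power at |r| of about 0.40 with 48 patients and 0.43 with 40. These figures assume a single pre-specified pair at baseline. They do not apply to an index picked from several, and power falls to 55% if the true correlation is 0.3. It should be corrected before results are seen.

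**What to change.** 1. **Reconcile the objectives in the Introduction with 2.10 and 2.5.3.** One way: make the between-group comparison on the listed clinical primary outcomes at 3 weeks the primary objective, with VAS as the sizing outcome, and the connectivity-synergy association a secondary mechanistic objective. Disability, depression and anxiety keep their listed rank. State a hypothesis for pain and disability, which now have none.
2. **Add one connectivity measure to 2.10.2 and 2.11.3.** For example, the Fisher-z correlation of mean HbO between a pre-named DLPFC channel set and a pre-named M1 channel set in one named task.
3. **Name the tests.** Its baseline correlation with one named synergy measure (for example tVAF1), and its between-group change adjusted for baseline. Label other channels, tasks and metrics exploratory.
4. **State the precision.** One such correlation has 80% power for |r| of about 0.40 in 48 patients and about 0.43 in 40.
5. **Reconcile 2.5.3 and 3.2 on the healthy group.** If there is none, reword the hypothesis so that it does not claim abnormality or reduction.

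**Cost:** rewording and one variable derived from data already planned. Under the option in item 1, the mechanistic question loses its primary label. A separate matter to check at the same time: the printed formula has a one-sample or paired form. With 1.48 as an SD, a two-group VAS comparison at 90% power needs 35 to 36 per group, and 24 per group gives about 75-77%, so relabelling alone does not secure the stated power.
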